### Anthropometric measures

4.3

Anthropometric data collection will include measurement of participant's height (cm) and weight (kg). Protocol for the measurement of height and weight will be developed based on the measurement techniques within the International Standards for Anthropometric Assessment published by the International Society for the Advancement of Kinanthopometry [38] and will be provided to the participants prior to the baseline teleconsultation. Participants will be asked to report their height (recorded to the nearest 0.1 cm) during baseline teleconsultation. They will be asked to measure their height using a portable height board and to remove any footwear or headgear while measuring their height. Weight (recorded to the nearest 0.1 kg) will be reported at three time points, baseline, six and twelve weeks. Participants will be advised to use the same weighing scales for the duration of the study and to weigh themselves at the same time of the day (in the morning preferably) and with minimal clothing. All participants are advised to repeat the process three times and to calculate the average to ensure accurate measurements. Whenever possible, anthropometric measurements must be performed in the presence of another person able to assist.

## Data management

5

The study RD will be responsible for the secure storage of participant data. Study data will be pseudo-anonymized and archived in a password-protected database. At each data collection time point, data are directly entered by the RD into an online cloud-based clinical data platform (Castor Electronic Data Capture (EDC)) hosted on secure servers. Study data will only be accessible to the coordinating and principal investigators.

## Sample size

6

The sample size calculation was based on the primary outcome measure. To detect a difference of 0.68 units (clinically relevant) in HAQ-DI [43] with 80% power and α = 0.05, 40 participants are needed in total. Adjusting for a potential 10% dropout, the sample size was determined to be 44 participants.

## Statistical analysis

7

Data will be transferred from Castor EDC into a Microsoft excel spreadsheet, cleaned and imported into SPSS for coding and analysis. Primary outcomes will be analysed based on an ‘intention-to-treat’ principle. Descriptive statistics (M, SD, N and %) will be used to explore demographic and personal characteristics and dietary intakes of participants. Independent samples t-tests and chi-square tests will be used, as appropriate, to investigate any differences between males and females, and to examine diet adherence scores at baseline. Independent t-tests and non-parametric alternatives will be used to assess differences between the two diet groups. The threshold for statistical significance will be set to p = 0.05.; SPSS version 25 will be used for statistical analyses. Differences in outcomes for the two groups will be compared while adjusting for potential confounders such as age, medications and other lifestyle factors.

The focus groups will be audio-recorded and transcribed verbatim. According to Braun and Clarke (2013), data analysis method comprises seven steps: transcription, reading, coding, searching for themes, reviewing themes, defining themes, and finalizing [44]. The transcripts will first be read and coded by two independent investigators. Codes will be compared and discussed to reach consensus. Thematic analysis will be used to inductively code themes that appear significant. Defined themes will then be grouped into categories, as either a perceived barrier or enabler. A second analysis will follow to compare between themes across the two different intervention groups. Analysis of data will mostly be descriptive.

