### Study design

2.1

The MEDRA study is a 12-week, parallel group, randomised controlled trial comparing two dietary interventions for the management of RA. This trial is designed in accordance with and adheres to the Consolidated Standards of Reporting Trials (CONSORT) statement [30]. Study participants will be randomly allocated to either a MedDiet group or the HEG group. Participants from both arms will attend five teleconsultations in total with the study Registered Dietitian (RD) over the 12-week intervention period on weeks 0, 3, 6, 9 and 12. For this study, blinding to intervention will not be possible but every effort will be made to manage participants in both groups as equally as possible. The primary endpoint is an improvement in physical function and quality of life of participants over the study period. The study design is detailed in Fig. 1.

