### Physical function and quality of life

4.1

The Rheumatoid Arthritis Quality of Life instrument (RAQoL) is the first patient-completed instrument specifically designed for use with people with RA. It entails 30 questions and respondents are required to indicate whether each of the questions applies to them. Scores range from 0 to 30, with a high score representing poor quality of life [33]. The Health Assessment Questionnaire – Disability Index (HAQ-DI) will monitor changes in the physical function of participants [34]. It is a self-administered questionnaire with 20 questions designed to estimate a patient's level of upper and lower extremity functioning. The total HAQ-DI score is calculated by summing the highest score in each of the 8 domains and dividing the sum by 8, yielding a score ranging from 0 (no disability) to 3 (severe disability). Participants will be required to complete the RAQoL and HAQ-DI questionnaires at baseline, six and twelve weeks.

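### The t-tests named for the diet comparison do not by themselves deliver the declared intention-to-treat analysis when week 12 questionnaires are missing

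*Protocol article*

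**What the plan says.** Section 7 (Statistical analysis) makes three statements that bear on the primary comparison.

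- The principle: "Primary outcomes will be analysed based on an ‘intention-to-treat’ principle". It is not defined further.
- The test: "Independent t-tests and non-parametric alternatives will be used to assess differences between the two diet groups". No visit is named, and the text does not say whether raw scores or changes are compared.
- An adjusted comparison: "Differences in outcomes for the two groups will be compared while adjusting for potential confounders such as age, medications and other lifestyle factors". No model is named.

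Section 4.1 sets the measurement times for both primary outcomes: "Participants will be required to complete the RAQoL and HAQ-DI questionnaires at baseline, six and twelve weeks". Table 1 agrees. Section 2.1 describes the endpoint without a time point: "The primary endpoint is an improvement in physical function and quality of life of participants over the study period".

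Section 6 (Sample size) gives the target, "To detect a difference of 0.68 units (clinically relevant) in HAQ-DI", "with 80% power and α = 0.05, 40 participants are needed in total", and then the allowance for loss: "Adjusting for a potential 10% dropout, the sample size was determined to be 44 participants".

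The article mentions no imputation, no repeated-measures model and no other handling of missing scores.

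**The concern.** An independent t-test or a rank test can use only people who have the value being tested. Applied at week 12 without imputation, it leaves out anyone with no week 12 questionnaire and gives no role to the score that person supplied at week 6. The principle and the named test therefore part company as soon as week 12 data are missing, and the plan expects some to be missing.

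The setting makes this worth settling in advance. The trial is unblinded, both primary outcomes are self-reported, and leaving may depend on the assigned diet and on how the participant is doing. If that dependence differs between the arms, an available-case comparison is biased. The result would still carry the intention-to-treat label.

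The order of events in section 3.1 adds a smaller risk. Participants are randomised first and then invited to complete the online questionnaires, so a randomised person can lack a baseline score. A t-test on change scores would drop that person as well.

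**Working it through.** **Inputs from the article.** Target difference 0.68 HAQ-DI units, power 80%, α = 0.05, 40 needed, 10% dropout, 44 recruited (section 6). Allocation 1:1 (section 3.1), so 22 per arm. Scores at weeks 0, 6 and 12 (section 4.1, Table 1).

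**Assumptions.** Two-sided α, the SD, the week 6 to week 12 correlation and the dropout mechanism. The article gives none of these.

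**1. The plan's own figure.** 40 × 1.10 = 44, which reproduces the stated total. (Dividing instead, 40 / 0.90 = 44.4, gives 45; the difference of one is immaterial here.)

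**2. How many would be missing.** 44 × 0.90 = 39.6. So about 40 would have a week 12 score and about 4 would not enter an un-imputed week 12 test.

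**3. An SD to work with.** The article states none, so the 40 cannot be rebuilt directly. Solving backwards for 20 per arm, two-sided 0.05 and 80% power, the t-test needs a standardised difference of 0.909, so SD = 0.68 / 0.909 = 0.75. The normal approximation gives 0.68 / [(1.960 + 0.842) × √(2/20)] = 0.77. I use 0.75.

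**4. Size of the bias.** Simulation of 400,000 people per arm with no true effect, SD 0.75 and correlation 0.7. Everyone has a week 6 score, and dropout follows it. Outside the random case, the log-odds of dropout change by 1 per SD of the week 6 score. Two estimates of the week 12 difference are compared:

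- available-case: the difference between arms in the mean of the observed week 12 scores;
- using week 6: in each arm, observed week 12 mean + b × (week 6 mean of all − week 6 mean of those observed at week 12), where b is the slope of week 12 on week 6.

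| Dropout pattern | 10% | 20% | 30% | Using week 6 |
|---|---|---|---|---|
| Random | 0.00 | 0.00 | 0.00 | 0.00 |
| Same dependence in both arms | 0.00 | 0.00 | 0.00 | 0.00 |
| Dependence in one arm only | 0.05 | 0.09 | 0.13 | 0.00 |
| Opposite dependence in the two arms | 0.10 | 0.18 | 0.27 | 0.00 |

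The three middle columns give the absolute bias of the available-case estimate in HAQ-DI units. At 10% dropout the largest value, 0.095 before rounding, is 0.095 / 0.68 = 14% of the target.

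**5. An unfavourable case by hand.** Put all four expected dropouts in one arm of 22, and let them score 0.5 worse than those who remain (assumed; range 0.3 to 0.8). The observed mean of that arm then looks better by 4/22 × 0.5 = 0.09 (4/22 × 0.3 = 0.05 to 4/22 × 0.8 = 0.15). That is 8% to 21% of 0.68.

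**6. Precision.** With SD 0.75, t-test power for 0.68 is 83.8% with all 44, 80.0% with 40 and 75.5% with 36. A model that uses week 6 scores can recover only part of what is lost.

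**The case against.** The strongest reply is that the conflict exists only if nothing is done about missing scores before the test. Imputing and then applying a t-test in the allocated arms would satisfy both sentences. Missing-data handling is commonly left to an analysis plan or full protocol, and neither is shown. That stands as a limit on what can be claimed: silence on imputation is not the finding. What remains is that the article itself pairs a principle with a test, and the test as written does not deliver the principle when scores are missing.

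A reader might go further and infer that the plan excludes dropouts, discards week 6 data and will report a completer analysis. The documents do not support this, for four reasons.

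- No visit is named for the t-test, and a week 6 test would use the week 6 data. Nothing says that those data are discarded or that dropouts are excluded.
- Someone who stops the diet but returns the questionnaires stays in the test, in the allocated arm. The right term is available-case. Nothing in the article says that questionnaires stop when the diet stops.
- The adjusted comparison needs something beyond a t-test and might be a repeated-measures model. Because its form is not given, it neither creates nor clearly resolves the problem; an ordinary regression of week 12 scores would lose the same people.
- Raising 40 to 44 is a routine allowance for lost information. It is consistent with analysing about 40 people but does not define the analysis set.

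The hand calculation in step 5 is also fairly called extreme. If dropout were unrelated to arm, all four would fall in the same arm with probability 2 × C(22,4) / C(44,4) = 0.108, and the top of the assumed range, 0.8, exceeds the target difference itself. Both arms receive active advice and the same contact schedule, so the article gives no specific reason to expect lopsided loss.

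**Conclusion.** The point holds in a limited form. The named tests are available-case unless data are imputed first. At the planned dropout about 4 of 44 randomised participants would not contribute at week 12, and their week 6 scores would not inform that comparison.

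The likely bias at 10% dropout is modest, between 0.00 and about 0.10 HAQ-DI units. It rests on an assumed SD of 0.75, a correlation of 0.7 and dropout after week 6 that depends on the week 6 score. It vanishes if dropout is random or acts alike in both arms. It reaches 0.27 at 30% dropout when the dependence runs in opposite directions in the two arms. I would make the change, because a better method is available from data already being collected, but this is not a defect that undermines the trial.

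**What to change.** Name the week 12 between-group difference as primary. Estimate it from one mixed model for repeated measures on the scores at weeks 0, 6 and 12, for HAQ-DI and likewise for RAQoL. Include group-by-visit terms, either adjust for baseline or constrain the baseline means to be equal, and apply a small-sample degrees-of-freedom correction. Every randomised participant with any score enters in the allocated arm. Constraining the baseline means has the advantage of keeping someone who has a later score but no baseline.

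State that the week 6 and week 12 online questionnaires are still requested from people who stop the diet. Add one sensitivity analysis that worsens the missing values in the MedDiet arm.

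The cost is a change of analysis wording, slightly more analysis work and the questionnaire links; it needs no extra participants or visits. The limit is that the model removes bias only as far as the observed scores explain dropout. Someone who leaves before week 6 contributes at most a baseline score, which is why the sensitivity analysis is needed.

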## Ethics and dissemination

8

Approval to carry out the study was obtained from the Health and Safety Executive (HSE) Mid-Western Regional Hospital Research Ethics Committee (REC Ref 103/19) and from the Education and Health Sciences Research Ethics Committee at the University of Limerick (2020_09_05_EHS). The study will be conducted in accordance with the Good Clinical Practice (GCP) guidelines and written informed consent will be obtained from all study participants. The consent form will contain all the information participants will need to know about participating in the study. They will also be asked if they wish to be involved in the focus groups at the end of the intervention period which are an optional part of the study. There are no additional incentives provided for participation in this trial.

Dissemination of study findings will take place through publications, seminars, blogs and written relevant information to patient organisations. Individual results will be made available to participants upon their request to the study RD.

## Discussion

9

Despite remarkable advancements in the pharmacological treatments of RA, other management approaches are commonly sought by individuals living with the condition [11,45]. There is a small number of randomised controlled trials and very little evidence on diet and RA. Having a better understanding of the impact of dietary interventions, as an approach for the management of RA will lead to development of dietary guidelines for this population. The MedDiet has been gaining popularity not only in the scientific literature, but also in clinical settings due to its many health benefits. While there is evidence to suggest that this dietary pattern is beneficial for inflammatory conditions, the evidence to recommend this dietary pattern for people with RA is still lacking. The proposed study aims to assess the effect of implementing a MedDiet among adults with RA in Ireland and to determine whether the MedDiet is superior to a standard healthy diet.

The MEDRA study has some limitations that need to be acknowledged. The intervention period is 12 weeks, this is a somewhat a short duration for a dietary intervention compared to other dietary interventions [46]. The sample size is small, and recruitment of study participants is conducted mainly through social media platforms so participants in the MEDRA study may represent a selected group of people with RA and potential selection bias must be evaluated. Further, while both primary outcome measures are clinically relevant, they are subjective measures and must be considered when interpreting results. Moreover, the fact that the MEDRA study is an unblinded study may introduce additional bias. The strength of this research is in its randomised controlled trial design. A trained RD is responsible for delivering both dietary interventions to ensure consistent high quality patient support. Focus group discussions at the end of the intervention will facilitate a deeper exploration into the enablers and barriers of the dietary interventions which is crucial for designing future interventions. Furthermore, the MEDRA study is carried out in collaboration with a consultant rheumatologist and, therefore, results may easily be shared with treating physicians in Ireland.

Most of the studies evaluating the efficacy of the MedDiet were conducted in Mediterranean populations [47]. As such, it is necessary to explore whether such an intervention is effective and in non- Mediterranean countries and among non-Mediterranean populations. To our best knowledge, the MEDRA study is the first randomized controlled trials assessing the effect of a MedDiet in an RA population in Ireland. The MEDRA study will provide evidence as to whether a dietary intervention can improve physical function and quality of life in adults living with RA. Given that the key elements that constitute the MedDiet such as fish, fresh fruits and vegetables, legumes, whole grains and extra virgin olive oil are all readily available and accessible in Ireland, the study will provide insights into the possibility of incorporating these components in an Irish context for people with RA. This, in turn, infer the potential translation to other inflammatory conditions.

## Ethics approval and consent to participate

The MEDRA study has been approved by the Education and Health Sciences Research Ethics Committee at the University of Limerick (2020_09_05_EHS) and by the Health Service Executive Mid-Western Regional Hospital Research Ethics Committee (REC Ref 103/19).

Informed written consent is obtained by all participants prior to commencing the study.

## Data statement

Data sharing is not applicable to this article as no datasets were generated or analysed during the current study.

